**Results:**

The study will evaluate the effects of health interventions on obese pregnant women through primary outcomes (e.g., BMI, weight, adverse pregnancy outcomes) and secondary outcomes (e.g., physiological indicators, quality of life, mental health) using various statistical methods. The results will provide insights into the intervention's effectiveness and cost-effectiveness across different socioeconomic groups.

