In China, patients with obesity and chronic diseases face severe challenges. Internationally, interventions for patients with obesity and chronic diseases are often supported by professional medical teams and community health programs. In contrast, Chinese patients tend to rely on hospitals and themselves. In view of China, therapeutic lifestyle intervention combined with AI technology, as an innovative intervention, is easy to implement and cost-effective. Through AI technology, personalized lifestyle advice can be provided, monitoring patient health data and timely adjusting treatment options. This intervention not only facilitates patients to receive management at home, but also can deliver professional support to meet the needs of patients in the process of lifestyle change effectively and efficiently. Therefore, research targeting this area has important practical significance and urgency.

This study designed a randomized controlled study to propose an AI-driven therapeutic lifestyle change (AI-TLC) intervention. Through personalization, continuous tracking feedback, intelligent decision aid, evaluate the influence of AI-TLC intervention on health behavior and health outcomes of obese pregnant women, determine the applicability and universality of AI-TLC intervention, provide innovative, efficient, and personalized health intervention for obese pregnant women, and provide new perspectives and methods for related scientific research and clinical practice.

Specific objectives are:

Primary: Can the intervention program driven by artificial intelligence (AI)–facilitated therapeutic lifestyle changes effectively promote improvements in health behaviors and health outcomes among pregnant women who are overweight or obese?

Sub-question 1:

Do the effects of the intervention differ among pregnant women of varying ages and degrees of obesity?

Sub-question 2: From a cost-benefit perspective, which level of intervention is the most effective (human-only vs. AI-only vs. human + AI)?

Sub-question 3: What are the short-term, medium-term, and long-term effects of this intervention program? What mechanisms need to be added to achieve better long-term outcomes?

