#### 2.4.2 Secondary outcomes

The secondary outcomes encompass physiological indicators such as blood pressure and blood lipid profiles (including triglycerides, low-density lipoprotein (LDL), high-density lipoprotein (HDL), and very-low-density lipoprotein (VLDL) cholesterol levels), quality of life assessments, mental health evaluations, and lifestyle factors (dietary habits and physical exercise patterns). Secondary outcome measures (such as blood pressure, lipid levels, and quality of life) will be analyzed using multiple linear regression or logistic regression, controlling for confounding factors such as age and baseline BMI, to assess the independent effects of the interventions. Subgroup analysis will further explore the differences in intervention effects across subgroups defined by factors such as age and BMI classification, with interaction tests conducted to verify the robustness of the results.

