### 2.6 Statistical analysis

Participants' socio-demographics are presented as count and proportion, and the χ^2^ test was used to assess categorical variables. The continuous variables normally distributed were assessed by the student's *t*-test. The Fisher's exact or the chi-square test was adopted for categorical data, and statistical significance was set at *p* < 0.05. The main analysis was performed using generalized estimating equations (GEE) model. The GEE solved the problem of correlation of longitudinal data, utilizing the results of each measurement in the longitudinal data, which greatly reduces the loss of information (20). To clarify whether socioeconomic status affects the effectiveness of ILSM, we conducted several subgroup analyses for physiological health outcomes and health behaviors, and added the interaction terms to generalized estimating equations model to assess the interactions between time (at baseline, 3-month, 6-month, and 18-month) and group (intervention and control). We also used GEE to analyze the health benefits of intervention and control groups among participants with different socioeconomic status. Significance level of the associations in the final model was set at *P*-value 0.05. The data were analyzed using SPSS 20.0 (IBM Corporation, Armonk, NY, USA).

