Next are the differences with the existing literature. Notably, our cost-benefit analysis revealed that the AI-only intervention offered a scalable solution with moderate efficacy, whereas the combined AI+Manual group achieved the highest clinical impact. This contrasts with Perdomo et al., who emphasized surgical and pharmacological interventions as primary strategies for severe obesity (15). However, our results align with Sallam et al., where TLC combined with medication synergistically improved metabolic outcomes (20). Such parallels suggest that hybrid models (AI + human expertise) may bridge the gap between resource-intensive and purely automated interventions.

However, this study has the following limitations. First, despite the high coverage rate of smartphones in China, some patients may not be able to use them well, which may hinder the implementation and reduce the effectiveness of AI interventions. Second, for the collection of the primary and secondary outcomes, we primarily used questionnaire indicators, which may inevitably lead to recall bias. Third, due to the lack of balanced stratification, comparative analyses between subgroups may not be suitable if the sample size of each group is insufficient across groups (e.g., compare the differences and potential influencing factors of AI-TLC intervention effects in different age groups). Fourth, the short-term follow-up period (up to 3 months postpartum) precludes conclusions about long-term weight maintenance. Meta-analyses of lifestyle interventions for obese pregnant women indicate that postpartum weight retention remains a challenge beyond 12 months (35), emphasizing the need for extended follow-up in future studies. Additionally, socioeconomic disparities in AI accessibility—particularly among older or rural populations—may limit generalizability, necessitating stratified analyses in broader cohorts.

Despite these limitations, this study may provide a scientific basis for developing personalized and effective interventions to further improve the health behavior and health of obesity pregnant women. It is expected to provide a new perspective and effective approach to the management of obesity pregnant women.

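### Section 2.6 asks whether socioeconomic status changes the intervention effect but names no term that tests this; the only interaction named is time by group.

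*Protocol article*

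**What the plan says.** Section 2.6 makes GEE the main analysis and then gives the purpose of its subgroup work: "To clarify whether socioeconomic status affects the effectiveness of ILSM". It describes two steps. The first is a set of subgroup analyses for physiological outcomes and health behaviours, with interaction terms added to the GEE "to assess the interactions between time (at baseline, 3-month, 6-month, and 18-month) and group (intervention and control"). The second reads "We also used GEE to analyze the health benefits of intervention and control groups among participants with different socioeconomic status". The section writes out no term containing SES and no contrast between SES levels.

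Elsewhere, sub-question 1 in the Introduction asks "Do the effects of the intervention differ among pregnant women of varying ages and degrees of obesity". Section 2.4.2 (Secondary outcomes) plans for those modifiers: "Subgroup analysis will further explore the differences in intervention effects across subgroups defined by factors such as age and BMI classification". The same sentence goes on to promise a formal check of these differences by interaction tests. The Results paragraph of the Abstract announces findings on "effectiveness and cost-effectiveness across different socioeconomic groups". The Discussion warns that "comparative analyses between subgroups may not be suitable if the sample size of each group is insufficient across groups".

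**The concern.** Whether SES modifies the effect is a question about the difference between treatment effects at different SES levels. A time-by-group interaction answers another question: whether the arms diverge over time, averaged over SES. It can be large when SES plays no part, and near zero when the effect runs in opposite directions in two strata. Fitting GEE by SES level gives one effect per level but no test or interval for the difference between them. A reader of such output is likely to look for significance in one stratum and not in the other, which is not evidence of modification.

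At stake is the SES result announced in the Abstract: it could be claimed or dismissed on output that does not bear on it. A smaller issue is that the section presented as the main analysis carries only SES. The modifiers of sub-question 1 are handled under the secondary-outcomes heading, so it is unclear whether they will be examined for BMI, weight and adverse pregnancy outcomes.

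**Working it through.** The plan gives no figure for this analysis, so there is none to reproduce. The check has a structural part and a numerical illustration.

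**Inputs.** From 2.1.1: 40 women per arm, two-sided alpha 0.05, effect size 0.5. From 2.6: significance level 0.05. Assumptions, because the document does not give them: the 0.5 is in SD units; two SES strata of equal size (20 per arm per stratum); two arms compared at a time; one change score with SD 1.

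**1. What time by group measures.** Simulation with 20,000 runs, 40 against 40:

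| True effect in the two strata | Time by group rejects | Group by SES rejects |
|---|---|---|
| +0.5 SD and +0.5 SD (no modification) | 61% | 5% |
| −0.5 SD and +0.5 SD (strong modification) | 4% | 60% |

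The named term rejects often when SES does not matter and hardly ever in the second row, where SES matters a great deal. The group-by-SES term behaves as a test of modification should.

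**2. Discordance between strata when there is no modification.** If each stratum has probability p of significance, exactly one of two is significant with probability 2p(1 − p).
- No true effect: p = 0.05, so 2 × 0.05 × 0.95 = 0.095, about 10% (simulated 9%).
- Equal effect of 0.5 SD: noncentrality 0.5 × √(20/2) = 1.58 on 38 degrees of freedom gives p = 0.338, so 2 × 0.338 × 0.662 = 0.447, about 45% (simulated 45%).
- The maximum is 50%, at p = 0.5. At p = 0.9 it falls again, to 2 × 0.9 × 0.1 = 18%.

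**3. Power of the proper contrast.** The difference between two stratum effects has standard error √(4/20) = 0.447 SD. Power is Φ(δ/0.447 − 1.96):
- δ = 0.25 SD: 8%
- δ = 0.5 SD: Φ(1.118 − 1.960) = Φ(−0.842) = 20%
- δ = 1.0 SD: 61%

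The proper test therefore holds its 5% level but can detect only very large differences.

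**4. Arms and visits.** The term in 2.6 is written for one intervention arm and one control arm at baseline, 3, 6 and 18 months. Section 2.2 randomises to three arms, all receiving an intervention. Section 2.1 lists five assessments: about 12, 20, 28 and 36 weeks of gestation, and 3 months postpartum. The term cannot be fitted to this trial in its present form.

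**The case against.** The strongest reply has four parts.

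- Section 2.6 speaks of interaction terms in the plural, in a sentence whose purpose is SES, so a term involving SES may have been intended. That cannot be excluded. The point is therefore that the needed term is not named, not that the authors have ruled it out.
- A reader might infer that 2.6 will declare modification by comparing stratum p-values and so will report chance differences. The text does not say this. It states no decision rule, and separate fits are only the natural reading of the GEE sentence. The discordance figures show what can happen if readers make that comparison, not what the plan prescribes.
- A reader might also infer that sub-question 1 has no planned answer. The documents do not support that. Section 2.4.2 plans age and BMI-class subgroups with interaction tests, which is a valid method for exactly those modifiers. Its heading does not settle its scope either: 2.4.1, headed primary outcomes, also contains the cost-effectiveness analysis. Only the reach of 2.4.2 to the primary outcomes is unclear. Nor does SES contradict sub-question 1, since the Abstract announces it as an additional question.
- The Discussion already concedes that subgroup comparisons may be unsuitable, and detail on exploratory subgroups can be left to an SAP. The concession favours reporting estimates with intervals. It does not repair a named term that addresses the wrong question.

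**Conclusion.** The point holds in this form: 2.6 poses an effect-modification question about SES, and neither step it describes, as written, tests it. This follows from the structure of the model and needs no numerical assumption.

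The size is illustrative. With two equal strata of 20 per arm and no modification, significance differs between strata in about 10% of trials with no true effect and about 45% with a common 0.5 SD effect. The upper figure is close to the 50% ceiling and depends on the assumed split, on reading 0.5 as SD units, and on a single-visit, two-arm comparison. Repeated measures or unequal strata would change it. Power of about 20% for a 0.5 SD difference in effects rests on the same assumptions and means that any SES finding can only be exploratory.

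For sub-question 1 a valid method is planned; its scope needs one clarifying statement.

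**What to change.** In 2.6:
- Add the SES-by-group-by-time term to the GEE, with its lower-order terms, and base any statement on modification on that term alone.
- Report its estimates with 95% intervals, label them exploratory, and state that modification will not be inferred from stratum p-values.
- Write the term for the three randomised arms and the visits listed in 2.1, in place of the two-arm wording and the 3-, 6- and 18-month times.

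In 2.4.2, or by cross-reference from 2.4.1, state that the age and BMI-class interaction tests also apply to the primary outcomes, so that sub-question 1 is explicitly covered.

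The cost is wording and a little more analysis. Table 1 already collects age, education, occupation, income, height, weight and BMI at T-0, so no new data are needed. The intervals will be wide, and the report should say so.

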## 2 Methods and analysis

### 2.1 Study participants and sample size

The baseline assessment for this study will be conducted at approximately 12 weeks of gestation. Follow-up visits are scheduled at approximately 20, 28, and 36 weeks of gestation, as well as at 3 months postpartum (24–32 weeks post-delivery). Figure 1 presents the detailed flowchart of this study.

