### 2.2 Randomization

After recruitment, the research team will conduct a pre-enrollment assessment and post-enrollment informed consent with the participants and their families, followed by randomization grouping:

A comprehensive assessment will be conducted before the participants are enrolled, including structured questionnaires and clinical examinations.

The approved subjects were randomly divided into Manual intervention group, artificial intelligence intervention group (AI intervention group), artificial intelligence and artificial combined intervention group (AI & Manual intervention group). The specific randomization operation is as follows: This study uses a simple randomization method. Random number series were randomly generated by the study designer using the RANDBETWEEN formula in EXCEL. The project will divide the subjects into different groups according to the sequence, the intervention team will know the grouping results, and the subjects will not know the grouping results.

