### 2.4 Outcomes

#### 2.4.1 Primary outcomes

The primary outcomes of the study include maternal body mass index (BMI), maternal weight, and adverse pregnancy outcomes. The primary outcome measures (such as BMI, maternal weight, and adverse pregnancy outcomes) will be assessed using Repeated Measures ANOVA or Mixed Effects Models to evaluate the intervention effects. For long-term effect analysis, Generalized Estimating Equations (GEE) or Cox Proportional Hazards Models will be employed to assess the short-term, medium-term, and long-term impacts of the interventions. Cost-effectiveness analysis will be conducted using Quality-Adjusted Life Years (QALY) and Incremental Cost-Effectiveness Ratios (ICER) to evaluate the economic efficiency of different intervention measures, with sensitivity analysis performed to verify the robustness of the results.

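### The only group and time terms that section 2.6 gives for the GEE contradict the three-arm design and the visit schedule, and 2.4.1 and 2.6 together fix no single main model

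*Protocol article*

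**What the plan says.** Section 2.6 states: "The main analysis was performed using generalized estimating equations (GEE) model". That sentence names no groups and no visits. The group and time terms come shortly afterwards, in a sentence on socioeconomic status that opens "To clarify whether socioeconomic status affects the effectiveness of ILSM" and goes on to add interaction terms to the GEE in order to "assess the interactions between time (at baseline, 3-month, 6-month, and 18-month) and group (intervention and control"). The two-group wording then recurs: "We also used GEE to analyze the health benefits of intervention and control groups among participants with different socioeconomic status". ILSM is defined nowhere and appears nowhere else in the article. The same section assigns normally distributed continuous variables to Student's t-test.

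The design is different. Under 2.2, participants are "randomly divided into Manual intervention group, artificial intelligence intervention group (AI intervention group), artificial intelligence and artificial combined intervention group". Section 2.3 describes a lifestyle plan for each of these three arms. Section 2.1 puts baseline at about 12 weeks and continues: "Follow-up visits are scheduled at approximately 20, 28, and 36 weeks of gestation", followed by one visit given as 3 months postpartum, with 24–32 weeks post-delivery in brackets. The limitations paragraph of section 3 says follow-up runs to 3 months postpartum. Table 1 has six undated columns, T-0 to T-5.

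On the model, 2.4.1 says that the primary outcomes "will be assessed using Repeated Measures ANOVA or Mixed Effects Models to evaluate the intervention effects". It then names GEE or Cox models for short-, medium- and long-term effects. Sub-question 2 in section 1 asks "which level of intervention is the most effective (human-only vs. AI-only vs. human + AI").

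**The concern.** An analyst working from 2.6 finds a group factor with two levels, one of them an arm that does not exist, and a time factor with a level at which nobody is seen. The plan says nothing about how to turn three arms into two groups, so that choice would be made later, possibly with the data in view.

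The choice of model is open as well. Standard repeated-measures ANOVA drops any woman with a missed visit. Unweighted GEE generally needs data missing completely at random. A likelihood-based mixed model needs only missing at random. With 40 women per arm followed over several visits, these can give different answers, and the article does not say which one is the main result.

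**Working it through.** The plan has no figure of its own to reproduce here. The sample size calculation plays no part in this point. The check compares 2.6 with the design sections.

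**Arms.** 2.6 has two groups, intervention and control. The abstract, 2.1.1, 2.2 and 2.3 have three arms, none called control. Write the 2.6 terms as intercept, group, three time indicators (3, 6, 18 months) and three group-by-time products: 1 + 1 + 3 + 3 = 8 columns. If every participant is in an intervention arm, the group column equals the intercept and each product equals its time indicator. Four columns are duplicates, so the rank is 8 − 4 = 4, and neither the group effect nor the group-by-time effect can be estimated.

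Forcing three arms into two groups can be done in six ways: merge two arms against the third (3 ways) or drop one arm (3 ways). A merge estimates none of the three pairwise contrasts separately. A drop estimates one of the three.

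**Visits.** One month is 30.4375 / 7 = 4.348 weeks. Delivery at 40 weeks is an assumption, giving 40 − 12 = 28 weeks from baseline to delivery.

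| Visit | Weeks from baseline | Months from baseline |
|---|---|---|
| 20 weeks | 8 | 8 / 4.348 = 1.8 |
| 28 weeks | 16 | 16 / 4.348 = 3.7 |
| 36 weeks | 24 | 24 / 4.348 = 5.5 |
| 3 months postpartum | 28 + 13.0 = 41.0 | 41.0 / 4.348 = 9.4 |
| 24 weeks post-delivery | 52 | 52 / 4.348 = 12.0 |
| 32 weeks post-delivery | 60 | 60 / 4.348 = 13.8 |

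In the other direction, 3 months from baseline is 12 + 13.0 = 25.0 weeks of gestation and 6 months is 12 + 26.1 = 38.1 weeks. Neither is a scheduled visit. Eighteen months is 18 × 4.348 = 78.3 weeks, or 78.3 − 28 = 50.3 weeks after delivery. That is beyond the last visit on either reading of the postpartum window.

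This does not depend on the anchor. Counting from the start of gestation, the latest possible visit is at (40 + 32) / 4.348 = 16.6 months, still short of 18. Counting from delivery, 18 months lies further off still. Nor does it depend on the delivery week: from baseline, a visit 32 weeks post-delivery would reach 18 months only if delivery came 78.3 − 32 = 46.3 weeks after baseline, at 58.3 weeks of gestation.

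**Size of the mismatch.** The interaction in 2.6 has (2 − 1)(4 − 1) = 3 degrees of freedom. Three arms at the five visits of 2.1 give (3 − 1)(5 − 1) = 8, or (3 − 1)(4 − 1) = 6 if baseline enters as a covariate.

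**Main model.** 2.4.1 gives repeated-measures ANOVA or mixed models for the primary outcomes, and GEE or Cox for effects over the short to long term. 2.6 gives GEE as the main analysis. GEE appears in both sections, but neither says which model yields the main result for which primary outcome.

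**The case against.** The strongest reply is that the mismatched terms belong to a socioeconomic analysis, whereas the main-analysis sentence names only GEE. That is correct. A reader might infer that the main analysis is itself written for two groups, or that it cannot be run. The documents do not support this: GEE runs perfectly well with a three-level arm factor and the real visits. What remains is that these are the only group and time terms 2.6 gives for the GEE. The interaction they describe is time by group, with no socioeconomic term in it, so an analyst has nothing else to work from.

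Other stronger readings also fail.

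- A reader might conclude that Sub-question 2 becomes unanswerable. It is posed in cost-benefit terms, and 2.4.1 gives it a separate QALY and ICER analysis. Only the three-way comparison of effects in 2.6 is lost.
- A reader might say the trial needs an untreated arm. An active comparator is a legitimate design, and the discussion frames the comparison as one against manual-only care.
- A reader might put a size on the bias: if both AI arms were merged and only the combined arm worked, a 0.5 SD effect would be estimated as (0 + 0.5) / 2 = 0.25 SD. No passage plans that merger or assumes that AI alone has no effect, so this illustrates one misreading and does not measure an error in the plan.
- The stray ILSM suggests text carried over from another study. That is an inference, and the point does not need it.

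Some of the reply stands in part. The 3- and 6-month labels lie loosely near 28 weeks (3.7 months) and 36 weeks (5.5 months). If months were counted from delivery, the single postpartum visit could fill one of the two labels, but the visits during pregnancy would then have no place. The t-test follows the description of socio-demographics and could be applied pairwise, so it is a secondary matter.

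The condensed format of an article is no answer, because these are statements that contradict the design and not details left to another document.

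**Conclusion.** The point holds as a contradiction inside the article. The group and time terms in 2.6 describe two groups with a control, at baseline, 3, 6 and 18 months. The trial has three active arms and ends with one postpartum visit. The absence of 18-month data is certain under every anchor and both readings of the postpartum window; the month figures in the table assume delivery at 40 weeks. The mismatch of the 3- and 6-month labels assumes counting from baseline.

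As written, the group and group-by-time terms cannot be fitted without improvising a control and merging or dropping an arm. Any such step recovers at most one of the three pairwise effect comparisons. Separately, 2.4.1 and 2.6 leave the main model open among candidates that handle missed visits differently.

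The defect is a mis-specified and unsettled model, not an unusable method or a faulty design. It should be corrected before analysis begins.

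**What to change.** - In 2.6, replace the group and time terms with a three-level arm factor, the scheduled visits and, for outcomes measured repeatedly, arm-by-visit. For weight and BMI, add the baseline value as a covariate.
- Reconcile the visit list in 2.1, including the two descriptions of the postpartum visit, with T-0 to T-5 in Table 1.
- Pre-name all three pairwise contrasts: AI versus manual, AI + manual versus manual, and AI + manual versus AI.
- Reconcile 2.4.1 and 2.6 to one named main model per primary outcome, with any alternative labelled as a sensitivity analysis. One workable choice is a linear mixed model for weight and BMI, which 2.4.1 already allows, and a binary-outcome model for adverse pregnancy outcomes. Keeping GEE as the main model would also resolve the conflict if both sections said so.
- Use the same three-level arm factor in the socioeconomic analyses.
- Replace the t-test with a three-group comparison, and delete ILSM, the control label and the 3-, 6- and 18-month labels.

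The cost is rewriting text in 2.6 and 2.4.1, and labelling the columns of Table 1. It needs no new data, participants or visits.
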